### Study design and conceptual frameworks

We propose a multicenter two-arm cluster randomized controlled trial that will employ a mixed-methods approach. This study will be guided by two conceptual frameworks, the Dynamic Adaptation Process (DAP) and the Reach, Effectiveness, Adoption, Implementation, and Maintenance (RE-AIM) framework, and will be carried out in three phases (Fig. 1). The DAP framework was developed to provide the structure for an iterative process to guide, monitor, and evaluate the introduction of a new intervention into practice. DAP is a framework that allows changes to be made according to the real context by the possibility of tailoring the elements of the intervention based on data obtained during the pre-implementation and the adaptation. DAP engages stakeholders at all levels to develop robust implementation strategies and will guide the work of phases one, two, and three in our study [29]. *Phase one* (pre-implementation) will consist of a formative baseline evaluation of the current situation for antibiotic prescribing for URTI in the outpatient setting among PLHIV and occur over three months. It will consist of interviews with identified health workers to understand the current antibiotic prescribing practices for URTI among HIV-infected ambulatory patients, as well as perceived facilitators and barriers to the roll-out of our de-implementation strategy. A document review will be performed to identify the existence of national guidelines or normative documents driving antibiotic prescribing for URTI. Phase one will also include documentation of current laboratory diagnostic capacity for URTI and a situational assessment of the availability of medicines to treat URTI. *Phase two* (adaptation and implementation) consists of our de-implementation strategy roll-out and will occur over six months. Based on information learned in phase one, we will make workflow adjustments to address realities on the ground. The CDSA will be rolled out within a two-arm cluster randomized control trial design in which our primary outcome measure will be the clinical decision to use antibiotics or not. Intervention elements and study tools will be adapted before the intervention is implemented. Throughout this phase, an implementation audit and continuous feedback will be conducted to guarantee and monitor adherence to the intervention protocol. *Phase three* (post-implementation) will consist of a three-month post-implementation phase in which we will analyze implementation outcomes and processes as a function of the RE-AIM conceptual framework, in real-time. *Reach* will be assessed in terms of patient recruitment, refusal, and attrition. *Effectiveness* will be analyzed by comparing antibiotic use rates and patient-related clinical outcomes between the intervention and control arms. For *adoption*, clinicians who adopted the practice of de-implementation of unnecessary antibiotic use will be assessed using prescriptions and clinical records. For *implementation*, the fidelity and satisfaction of clinicians regarding the intervention will be assessed. For *maintenance*, sites and clinicians that maintain de-implementation practices and use of the CDSA will be assessed one year after completion of the intervention.

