### Randomization within the two-arm cluster randomized trial and characteristics of the study participants

To mitigate contamination threat to internal validity among participating facilities, randomization and allocation will be primarily among the 10 administrative units (primary clusters). Primary clusters are considered municipal districts (Maputo) or administrative posts (Matola). Randomization will be performed before the initiation of our pre-implementation phase. Initially, randomization will be undertaken through the generation of a sequence of random numbers corresponding to each primary cluster. A total of six primary clusters will be randomly assigned to either the intervention or control arms (three each). Afterwards, in each selected primary cluster only one primary healthcare facility (secondary cluster) will be randomly selected to participate in the study. All participants in the same facility will be assigned to the same treatment, either intervention or control. A statistician will generate the allocation sequence and assign participating healthcare facilities to intervention or control groups.

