### Intervention and control

Eligible patients allocated to intervention will be managed using the CDSA. Eligible patients are adult HIV-infected with respiratory symptoms (nasal secretions or runny nose, congestion, sore throat, coughing, sneezing, chills, smell and taste disorders, with or without a fever) [30]. Adult HIV-infected patients without URTI symptoms, those with fever ≥ 39ºC, severe mental illness, or advanced HIV status will be excluded from the study. All PLHIV with URTI symptoms lasting less than 10 days will not receive an antibiotic unless there is an additional symptom suggesting a suspect of bacterial infection. Otherwise, bacterial infection will be suspected in the following situations: (i) higher-grade fever than normally observed with the common cold, with the presence of yellow or greenish nasal discharge, pain/difficulty swallowing, or an intense sore throat; (ii) URTI symptoms lasting longer than 10 days; (iii) URTI symptoms continuing to get worse rather than improve over several days (5 days after the first visit) [31].

Decongestants and/or antihistamines may be used to relieve symptoms of cough, congestion, and runny nose at the clinician's discretion [32]. Those with an increase in symptoms after five days, or a persistence of symptoms after 10 days, without systemic symptoms, will be treated with topical nasal steroids. If improvement of symptoms is observed after five days of treatment with nasal steroids, patients will continue with treatment for seven to fourteen days. Without improvement, consider 5 days of treatment with antibiotics. If improvement, patients should continue with treatment for seven to fourteen days. If symptoms get worse after 5 days of antibiotics, patients will be referred to an ear-nose-throat specialist (ENT). On the other hand, those with systemic symptoms without complications will follow five days of treatment with antibiotics, nasal decongestants, and topical nasal steroids (Fig. 3). Those with complications (acute otitis media, sinusitis, bronchitis, and pneumonia) will be given five days of treatment with antibiotics. Then, without improvement after 5 days of antibiotics, patients will be referred to an ear-nose-throat specialist. The promotion of de-implementation of unnecessary antibiotic use for HIV-infected patients with URTI symptoms lasting less than 10 days will be the core strategy of using the CDSA in the experiment arm.

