### Data collection and measures

Phase one (Pre-implementation)

Data for the study will be drawn from multiple sources. For phase one, we will collect qualitative data about the current context of both intervention and control sites regarding the treatment of URTI among outpatient HIV-infected patients. We will conduct in-depth interviews among relevant healthcare workers which will include clinicians, pharmacists, and laboratory technicians using interview forms to guide and collect data. Interviews will include a combination of close-ended and open-ended questionnaires to explore current antibiotics prescribing practices for URTI, current workflow of patients through the facility, management of work processes, existence of current practices and normative documents in performing prescription audits and feedback, existence of any initiatives for implementing an antimicrobial stewardship program (ASP), willingness to work as a team to change work processes, availability of medicines to treat URTI, and current laboratory capacity for diagnosing the etiology or a URTI.

Phase two (adaptation and implementation) and phase three (post-implementation)

Throughout phases two and three we will collect both quantitative and qualitative data. For each HIV-infected patient determined to be eligible for this study, we will collect information related to their socio-demographics, current symptoms, and management decisions related to antibiotics. If antibiotics are prescribed, we will collect data on the type of antibiotic, and expected length of treatment. Antibiotic prescriptions data will be collected from both pharmacy and medical records. To assess whether a clinician has adopted the de-implementation of unnecessary antibiotic use, the duration of symptoms and prescriptions will be reviewed in the clinical records. This will be measured as the proportion of clinicians who adopted the de-implementation of unnecessary antibiotic use practices among those who participated in the study. The “Reach” outcome will be measured as the proportion of patients in the target population reached by the intervention (in terms of # patients recruited, # patients refused and # patients recruited and dropped out during the intervention). This data will be collected from the study data record form.

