Qualitative data will be collected to measure the satisfaction of health workers regarding the implementation of the intervention including information related to adoption and acceptability of the intervention. This data will be collected through in-depth interviews with intervention site clinicians, using an interview guide and will be audio recorded. The interview guide will contain open-ended questions related to the adoption, fidelity, and acceptability of the intervention. An additional survey will be used to assess the degree of clinicians’ satisfaction. Maintenance will be measured as both the number of sites and clinicians that maintain the use of the de-implementation strategy one year after completion of the intervention implementation. This data will be collected from prescriptions and clinical records.

Secondary outcomes consist of the incidence of complications as a result of non-prescription of an antibiotic and the mean time for complete recovery from the first medical visit. This information will be collected from the study data record form. The incidence of complications will be measured as the proportion of complications arising from non-prescription of an antibiotic among patients who did not receive antibiotics. The mean time for complete recovery will be measured as the average time that the patients took to recover completely from their symptoms.

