### Data management and statistical analysis

We will design our study forms in REDCap (Research Electronic Data Capture), a secure web data capture tool developed by Vanderbilt University that offers a range of functions to collect, store, and analyze basic data from the desired population. Forms will be stored and de-identified in REDCap with access to all study researchers and the REDCap data manager of the Faculty of Medicine of Eduardo Mondlane University. The forms will be exported to SPSS (Statistical Package for Social Sciences) version 25 for statistical analysis.

Quantitative data analysis

Descriptive and inferential statistical analysis deemed relevant based on collected data will be performed. The descriptive analysis will be based on the elaboration of absolute and relative frequency tables and charts. To explore the factors associated with antibiotic prescribing and the need for antibiotic prescribing, multivariate logistic regression analysis will be performed. The dependent variables to be considered separately will be the prescription of antibiotics and the need for the antibiotic. Each dependent variable will be crossed with the possible factors (independent variables). ANOVA will be used to test differences among sites within the same group for both intervention and control sites with a significance level of 5%.

To compare the effect of the intervention between the intervention and control sites, Pearson's chi-square test will be used, with a significance level of 5%. To verify the magnitude of the effect of the intervention, the relative risk (RR) will be calculated and to estimate the effectiveness of the intervention, the effectiveness ratio (1 – RR) will be determined. For inferential analysis, the 95% confidence interval will be calculated for the RR parameter.

For power calculation, we have set alpha equal to 0.05 and 80% power to detect differences in proportion greater than or equal to 0.15. In other words, if we get a reduction of 15% of the overall antibiotic rate in the intervention sites compared to control sites, we could detect a significant change in proportion. We assumed a coefficient of variation equal to 0.2 for this estimate.

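### The intervention effect is fixed as an unadjusted chi-square and RR, although the presenting symptoms that drive prescribing are collected and three facilities per arm cannot be relied on to balance them

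*Protocol article*

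**What the plan says.** All references are to the protocol article.

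- **Outcome** (Study design and conceptual frameworks): "our primary outcome measure will be the clinical decision to use antibiotics or not".
- **Arm comparison** (Data management and statistical analysis): "Pearson's chi-square test will be used, with a significance level of 5" per cent. For the effect estimate, "To verify the magnitude of the effect of the intervention, the relative risk (RR) will be calculated", followed by 1 - RR and a 95% confidence interval. No covariate, stratification or standardisation is attached.
- **Regression on prescribing** (same section): "To explore the factors associated with antibiotic prescribing and the need for antibiotic prescribing, multivariate logistic regression analysis will be performed". Study arm is not named as a term, and this model is not the effect estimate. The other regression in the plan concerns clinicians' satisfaction.
- **What drives the decision** (Intervention and control): "All PLHIV with URTI symptoms lasting less than 10 days will not receive an antibiotic unless there is an additional symptom". The grounds for suspecting bacterial infection are fever with discharge or throat symptoms, duration beyond 10 days, and worsening after the first visit.
- **What is collected** (Data collection and measures): "we will collect information related to their socio-demographics, current symptoms, and management decisions related to antibiotics".
- **Allocation** (Randomization section): six areas are randomised, three per arm, with one facility drawn from each. No matching, stratification or constraint on case mix is described.

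**The concern.** The outcome is a prescribing decision, and the protocol itself names symptoms as the grounds for that decision. A facility that happens to see more patients with those symptoms will prescribe more whatever its arm. With many clusters such differences average out; with three per arm they may not. The planned RR takes the whole of that difference as intervention effect.

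Two things are at stake. The single allocation that is drawn may carry a case-mix difference that is sizeable against the 15-point target. And the part of between-facility variation that known symptoms explain stays in the error, in a trial with very few facilities. The plan states its method here, so this is a choice that can be improved and not a detail left to an analysis plan.

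**Working it through.** **The plan's own figure.** It gives none for case mix. Its 190 per arm can be approached only roughly. With 65.9% (Background) against 50.9%, two-sided 5% and 80% power, individual randomisation needs 169 per arm, or 182 with continuity correction. Reaching 190 takes steps the article does not state. The point below does not depend on it.

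**Inputs from the article.** Three facilities per arm; 380/6, about 63 patients per facility; target difference 0.15.

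**Assumed inputs.** 30% of patients have a symptom picture that prompts antibiotics. Control prescribing is 90% with it and 50% without. The share varies between facilities with SD s = 0.05, 0.10 or 0.15. The last is already extreme, since 0.30 ± 1.96 × 0.15 runs from 0.01 to 0.59. Other facility variation has SD u = 0.08 (assumed), or 0.13 if the stated coefficient of variation of 0.2, which the article does not define, is read as between-facility: 0.2 × 0.659 = 0.13. The effect is 15 points in both symptom groups.

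**Formulas for the variance of the arm difference.**

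- Case mix: V_mix = (0.90 - 0.50)² × (2/3) × [s² + (0.21 - s²)/63].
- Everything else: V_rest = (2/3)u² + W/(3 × 63).
- W is the within-facility variance given symptoms, summed over arms. Control: 0.3 × 0.09 + 0.7 × 0.25 = 0.2020. Intervention (75% and 35%): 0.3 × 0.1875 + 0.7 × 0.2275 = 0.2155. So W = 0.4175 and W/189 = 0.00221.
- Crude SD = √(V_mix + V_rest). Adjusted SD = √V_rest, treating the symptom coefficients as known.

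For u = 0.08, V_rest = 0.00427 + 0.00221 = 0.00648, so the adjusted SD is 0.0805. For u = 0.13, V_rest = 0.01127 + 0.00221 = 0.01348, so it is 0.1161.

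| s | SD of arm difference from case mix alone | Chance it exceeds 5 points | u = 0.08: SD crude to adjusted | Power (t, 4 df) | u = 0.13: SD crude to adjusted | Power (t, 4 df) |
|---|---|---|---|---|---|---|
| 0.05 | 2.5 points | 4% | 0.084 to 0.081 (-4%) | 28% to 30% | 0.119 to 0.116 (-2%) | 17% to 17% |
| 0.10 | 3.7 points | 18% | 0.089 to 0.081 (-9%) | 26% to 30% | 0.122 to 0.116 (-5%) | 16% to 17% |
| 0.15 | 5.2 points | 34% | 0.096 to 0.081 (-16%) | 23% to 30% | 0.127 to 0.116 (-9%) | 15% to 17% |

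**Sensitivity to the predictor.** With prescribing of 95% against 53.4% and s = 0.15, the falls are 17% and 9%. With 85% against 57.7% and s = 0.05, they are only 2% and 1%.

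**Simulation check** (6,000 trials per setting, facility residuals compared on 4 df). For u = 0.08 the SD falls from 0.088 to 0.079 (s = 0.10) and from 0.094 to 0.078 (s = 0.15, -17%). Power rises from 23-27% to 29-31%, and type I error stays near 5%. Comparing log observed/expected ratios instead gives 26-29%. For u = 0.13 and s = 0.10, power is about 16% crude, 17% with residuals and 15% with log ratios.

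**One realised imbalance.** A 10-point difference between arms in the symptom share moves the crude difference by 0.10 × (0.85 - 0.577) = 2.7 points to 0.10 × (0.95 - 0.534) = 4.2 points. That is 18-28% of the 15-point target.

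**Under the planned chi-square.** If facilities differ only in symptom share (s = 0.10), its simulated type I error is 7.5-11.1%, against 4.9-5.1% when stratified on the symptom picture. With other variation at SD 0.13 it is about 40% either way, so adjustment alone does not repair the test.

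**The case against.** An unadjusted primary comparison with adjusted sensitivity analyses is a legitimate choice, and covariate lists commonly sit in an analysis plan. The article does plan a regression on prescribing and, in the abstract, promises to examine site and patient factors. That stands in part: the exploratory model could be turned into an adjusted effect analysis. As written it is not one, and the effect estimate is named as crude.

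The size is also open to challenge. No passage gives the symptom share, its spread or its link to prescribing. The Background calls most infections viral and current prescribing predominantly empirical, so symptoms may predict control-arm decisions less well than assumed. This stands, and it is why the gain is given as a modest range.

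Four stronger readings are tempting and are not supported:

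- **That the crude RR is biased.** Chance imbalance under randomisation is imprecision. A correct cluster-level interval would cover it.
- **That adjustment would cure selective recruitment.** Clinicians identify patients after allocation, at sites that know their arm, and symptoms are recorded at that same stage. Adjusting for them does not reliably remove such a difference and could add to it.
- **That every needed covariate is already on the study form.** For patients the article lists current symptoms. Symptom duration is mentioned only as something reviewed in the clinical records.
- **That the recovery outcome has the same stated flaw.** It is defined as "the mean time for complete recovery from the first medical visit", but no arm comparison is specified for it. That is silence, not an error.

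**Conclusion.** The point holds as a matter of precision and chance imbalance. The plan fixes a crude comparison, although it intends to collect strong candidate predictors of the outcome and randomises too few facilities to rely on balance.

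The benefit of adjusting is modest: about 4-17% off the SD of the estimate if other facility variation has SD 0.08, and about 2-10% with little power gain if it is 0.13. A weak link between symptoms and prescribing would bring it lower still. These figures rest on the assumed 30% share, prescribing rates and facility spread.

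The change is worth making because it is cheap, but it ranks below the omission of clustering from the same test and confidence interval.

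**What to change.** Prespecify a case-mix-adjusted effect estimate in two stages.

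1. Fit a patient-level model of the antibiotic decision on t0 symptoms, age and sex, without arm. Leave out worsening after the first visit, which is not a t0 value.
2. For each facility take observed minus expected prescribing, and compare the six residuals between arms with a t test and interval on 4 degrees of freedom. This respects the clusters and spends no facility degrees of freedom on covariates. The difference scale matches the target stated in the power calculation.

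Report observed/expected ratios and the crude RR as supporting. Include symptom duration only if it is recorded in the same way in both arms at t0. State that adjustment is for case mix and is no protection against differential recruitment.

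The cost is a paragraph in the analysis plan and a few lines of code, plus a check of how duration is recorded. Recruitment began in June 2024, so the covariate list should be fixed before outcomes are examined by arm.

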During phase one (pre-implementation), we will enroll 42 health workers as part of our formative baseline assessment. Eligible health workers will include clinicians, laboratory technicians, pharmacists, and health managers at each of our six study facilities. During phase two (adaptation and implementation), all clinicians at each site working with adult HIV-infected patients aged 18 years and older will be enrolled in the study. Eligible health workers are nurses, clinical officers (called *Técnicos de Medicina* in Portuguese), and physicians. Health workers attending to pediatric patients and those not engaged in the HIV outpatient clinic will be excluded from the study. One identified person (health worker or manager) from each cluster facility will function as a local coordinator, responsible for coordinating activities on site and being the contact between healthcare providers participating in the intervention and the research team. A sample of 380 HIV-infected patients with URTI will be enrolled and assigned to each study arm in a 1-to-1 ratio (190 for each arm) (Fig. 2). To achieve adequate participant enrollment, all clinicians who examine HIV-infected patients in the screening and outpatient consultation rooms at each selected health facility will be requested to identify potential participants among their patients, and the study team will invite them to participate in the study.

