**Fig. 2 Fig2:**
[figure not shown]
Study flow diagram: enrollment, intervention, and assessments

For phase three (post-implementation), we will re-interview all clinicians from each of the intervention sites concerning aspects of the intervention implementation and satisfaction.

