Quantitatively, satisfaction will be measured as the degree of satisfaction of the prescribing clinicians at the intervention study sites using the CDSA. To identify the factors that influence their degree of satisfaction using the CDSA, a multivariate logistic regression analysis will be performed. For the dependent variable, the satisfaction of clinicians, the 5-point Likert scale will be reduced to a binary category of dissatisfied (very dissatisfied, dissatisfied, neutral) and satisfied (very satisfied, satisfied). Potential factors that influence satisfaction to be considered are sex, age, length of time in current position, and the professional category of the health worker.

Qualitative data analysis

Qualitative data will be coded and analyzed using qualitative analytic software (*NVivo version 12*). Audio recordings will be transcribed and coded using constructs consistent with our study aims and relevant implementation outcomes (adoption, acceptability) which will be outlined in a codebook with definitions. After encoding the constructs, a directed content analysis approach with allowance for the emergence of new themes will be used. After the qualitative analysis, we will perform a quantitative analysis of the contents or themes using a frequency table to be created in the Excel program.

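### The satisfaction model fits about five slopes to an unstated number of clinicians at three facilities; with fewer than about 100 clinicians its adjusted odds ratios will be undefined or very imprecise

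*Protocol article*

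**What the plan says.** All references are to the protocol article.

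- **Population.** In the section on data management and statistical analysis, "satisfaction will be measured as the degree of satisfaction of the prescribing clinicians at the intervention study sites using the CDSA". Under the randomisation section, three clusters go to each arm and one facility is drawn per cluster, so there are three intervention facilities. After Fig. 2, for phase three, the article says "we will re-interview all clinicians from each of the intervention sites". No number of clinicians is given.
- **Outcome.** "the 5-point Likert scale will be reduced to a binary category of dissatisfied (very dissatisfied, dissatisfied, neutral) and satisfied (very satisfied, satisfied".
- **Model.** "To identify the factors that influence their degree of satisfaction using the CDSA, a multivariate logistic regression analysis will be performed".
- **Factors.** "Potential factors that influence satisfaction to be considered are sex, age, length of time in current position, and the professional category of the health worker".
- **Professional category.** The randomisation section names three eligible professions: nurses, clinical officers and physicians.
- **Only staff count.** For phase one, "we will enroll 42 health workers as part of our formative baseline assessment". These workers include laboratory, pharmacy and management staff and come from all six facilities.

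The software is SPSS version 25. No penalised or exact method, limit on the number of factors or descriptive fallback is attached to this model.

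**The concern.** A multivariable logistic model needs enough clinicians in the smaller outcome group (satisfied or dissatisfied) for each slope it estimates. Here the slopes can be counted and the data source is narrow: the adult HIV clinicians of three primary care facilities. If that group is small, some combination of factors will often split the satisfied from the dissatisfied perfectly or nearly so (separation). At least one odds ratio then has no finite estimate, and the software prints either a failure or an arbitrarily large value. Where the fit does converge, the intervals are too wide to interpret.

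At stake is one stated aim of the implementation evaluation, namely finding which clinician characteristics go with satisfaction. Satisfaction is part of the implementation dimension of RE-AIM, and the results are to go to the Ministry of Health.

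**Working it through.** The article gives no sample size, event count or power for this model, so there is no figure to reproduce. The number of clinicians (n) and the share satisfied (p) are assumptions and are varied.

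**Step 1: slopes.** Sex 1 + age 1 (linear) + time in position 1 (linear) + professional category 2 (three levels) = 5, plus an intercept. Grouping age or time into categories would add slopes.

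**Step 2: scale of n.** 42 health workers / 6 facilities = 7 per facility; 7 × 3 = 21. This count includes non-prescribers and is a phase-one interview sample, so it only suggests a scale.

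**Step 3: events per slope.** The approximation is n × min(p, 1 − p) / 5.
- n = 21: 21 × 0.5 / 5 = 2.1; 21 × 0.3 / 5 = 1.3; 21 × 0.2 / 5 = 0.8 (for 50%, 70% and 80% satisfied).
- n = 60: 6.0; 3.6; 2.4.

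At p = 0.5 the simulated means are a little lower (1.7 at n = 21 and 5.4 at n = 60), because the smaller group in a sample usually falls below half.

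**Step 4: how often no finite estimate exists.** There were 500 simulated datasets per cell. Sex was 50:50, age and time in position were normal with correlation 0.6, the three categories were 30/50/20%, and there were no true effects. Separation was detected by linear programming. Datasets with every clinician in one outcome category were also counted as having no finite estimate. The last column is the upper 95% limit divided by the lower limit for the sex odds ratio, taken as the median over datasets that could be fitted.

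| n | No finite estimate, p = 50 / 70 / 80% | Events per slope (simulated) | CI limit ratio, sex OR |
|---|---|---|---|
| 21 | 24 / 41 / 70% | 1.7 / 1.3 / 0.8 | 119 / 177 / 249 |
| 30 | 10 / 25 / 50% | 2.6 / 1.8 / 1.2 | 35 / 46 / 82 |
| 60 | 0 / 2 / 12% | 5.4 / 3.6 / 2.4 | 9 / 11 / 17 |
| 90 | 0 / 1 / 4% | 8.2 / 5.4 / 3.7 | 6 / 7 / 9 |

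A second simulation gave 33-71% at 21, 8-46% at 30 and 1-11% at 60 for 50-80% satisfied. Taken together the ranges are roughly 24-71%, 8-50% and 0-12%.

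**Step 5: clinicians needed.** n = 5 × (events per slope) / min(p, 1 − p). The targets of 5 and 10 events per slope are rules of thumb assumed here.
- 10 per slope: 50 / 0.5 = 100; 50 / 0.3 = 167; 50 / 0.2 = 250.
- 5 per slope: 25 / 0.5 = 50; 25 / 0.3 = 84; 25 / 0.2 = 125.

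Over three facilities, 100 clinicians is about 33 per facility and 50 is about 17.

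**Step 6: behaviour of the tests.** With no true effects and 12-21 clinicians, Wald tests flag at least one factor in only 0-8% of datasets. Likelihood-ratio tests flag one in about 33-43%. Four independent tests at 5% would flag one in 1 − 0.95⁴ = 19%. The article does not say which test will be used.

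Clustering of clinicians within the three facilities would reduce the information further and is not in these figures.

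**The case against.** The strongest objection is that the decisive number is not in the article. A reader might infer from the 42 health workers that the three facilities hold only about 12 to 21 clinicians. The article does not support that. The 42 are a phase-one interview sample of mixed staff, whereas satisfaction is measured in all prescribing clinicians at the intervention sites, so one does not bound the other. The result does depend on n and p: with an even split, separation falls to 1% at 45 clinicians and 0% at 60. This stands, and it is why the point is conditional. What remains is imprecision: at 60 clinicians the limits for the sex odds ratio still differ by a factor of 9 or more. A total near 100 also sits awkwardly with the 190 patients planned for the intervention arm, about two enrolled patients per clinician (190 / 100 = 1.9).

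A reader might also infer that spurious factors will routinely be declared significant. That is too strong. Under separation the standard errors grow with the estimates, so Wald tests become conservative. Only likelihood-ratio tests are inflated. The main harm is undefined or extreme odds ratios and an uninformative model.

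It is fair to add that the factors are called potential, so fewer might be entered, and that a fuller document may settle the details. But the article itself names the model, the population, the outcome and the factors, and gives no rule for reducing them. Frequency tables and in-depth interviews are also planned, so satisfaction will be described in any case. Only the question of its predictors is affected.

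**Conclusion.** The point holds in conditional form, as a minor one. The article commits to a mutually adjusted logistic model with about five slopes on the clinicians of three facilities, with no small-sample method. Unless there are about 100 or more clinicians (and more than that if satisfaction is well away from 50%), the adjusted odds ratios will be undefined or very imprecise and cannot identify what influences satisfaction.

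The conclusion rests on linear age and time in position, three professional categories, 50-80% satisfied, the simulated covariate mix and the events-per-slope rule of thumb. It does not rest on a known number of clinicians.

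The abstract lists implementation of the strategy among the primary outcomes, so a reader might infer that the trial's main result is at risk. It is not: the comparison of antibiotic prescribing between arms does not use this model.

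**What to change.** Make the main satisfaction analysis descriptive: the proportion satisfied with an exact 95% CI, plus the distribution of the full 5-point score by sex, professional category and time in position. State the number of clinicians expected at the three intervention facilities. If factors are modelled, take one at a time with Firth-penalised or exact logistic regression, and label the results exploratory.

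This changes analysis wording only and needs no new data. The cost is that there will be no mutually adjusted associations, which the data are unlikely to support unless the number of clinicians is far larger than the phase-one count suggests.
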